### Data collection and management

3.6

Data will be collected at baseline, midpoint (6 months) and endpoint (12 months). At baseline, we will collect data on antimicrobial use on animals (frequency and quantity used per month). At midpoint, we will obtain data on vaccination uptake, antimicrobial use, and farmer wellbeing. In addition, we will review the registers maintained by the veterinary officers and village leaders, and conduct in-depth interviews with the stakeholders to evaluate intervention fidelity, acceptability, and feasibility to scale-up. Data collected at endpoint will include the data collected at midpoint in addition to data on disease-related mortalities experienced over the 12 months. The data will be collected with Open Data Kit (ODK) application, and interviews recorded.

All livestock-owning households in the study area who are geographically accessible all year round are eligible to be included in the study. To be included, farmers need to own at least three (3) tropical livestock units (TLUs) of eligible ruminants i.e. ruminants that are at least 3 months old. One (1) TLU corresponds to 0.75 cattle and/or 0.1 small ruminants (sheep and goats) [29]. Caretaker farmers who do not own the minimum TLUs of the livestock in the herds kept will be excluded from the study.

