## Introduction

1

In low-and-middle income countries (LMICs), animal diseases are highly prevalent and poorly controlled due to low performance of veterinary services and limited farmer engagement, resulting in significant herd mortalities [1]. On average, about 7% of adult cattle, 21% of calves, 15% of adult sheep and goats, and 23% of lambs and kids die from animal diseases annually in the least developed countries [2]. In LMICs, majority of households are smallholders earning less than USD 60 monthly in agricultural income [3]. In contrast, the average market value of ruminant livestock in Africa ranges between USD 120 for one sheep or goat and USD 600 for one cattle [4]. The livestock losses negatively affects productivity of the livestock sector, livelihoods of farming households and contributes to food insecurity, particularly for vulnerable households in LMICs [5]. Disease-related mortalities also adversely affect farmers’ wellbeing, particularly on the psychological, physical, and social domains [[6], [7], [8]].

What is more, veterinary services delivery has been ineffective in many LMICs in practice, due to inadequate public investment in the veterinary sector, with significant shortfalls in human and material resources [9]. This lack of investments is often attributed to the implementation of drastic structural adjustment policies during the 1980s aimed at addressing high indebtedness levels of LMICs [10]. In addition, veterinary medicines are poorly regulated. A recent review showed that 80% of African countries lack capacity to control the registration, import and production, distribution and usage of veterinary medicines. There is also a lack of drug residue testing programmes in more than two-thirds of the countries [11]. Thus, an overwhelming majority of farms use antimicrobials regularly, without professional advice [12,13].

The high usage of antimicrobials coupled with a lack of residue testing programmes and inadequate regulatory capacity within the food chain, could foster the persistence of drug residues in livestock products, especially when treated livestock are slaughtered prior to recommended withdrawal periods, and accelerate the development of related antimicrobial resistant pathogens [14,15]. Given the apparent shortfalls in veterinary resources, a reduction in occurrence of diseases, particularly through disease prevention strategies, would greatly reduce the disease burden, and workload on veterinary personnel.

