### Study setting

3.1

This study will be conducted in the Mion, Pru East and Kwahu Afram Plains South (KAPS) Districts, which are representative of the northern, middle and southern farming belts of Ghana. The districts lie in the Guinea Savannah, Transition and Deciduous forest Vegetation zones, which are the primary livestock production zones in Ghana [[23], [24], [25]]. The districts were selected purposively in collaboration with the regional directors of veterinary services, using a sampling frame of farming districts located within these vegetation zones. The selected districts are mainly rural and agrarian, with about one-third of the livestock holdings of households being ruminant species. Cattle, sheep, and goats are the predominant ruminant livestock species reared in these districts. Majority of livestock rearing (53%) is for income generation – the rest is directly consumed by households, or used for other socio-cultural purposes. The livestock production system is largely extensive and dominated by small-scale farmers [26].

In rural Ghana, livestock farmers typically obtain approval from community leaders such as chiefs, local assembly members, landowners, or opinion leaders, to keep and graze their animals within the community [27]. Veterinary services in these areas are predominantly provided by veterinary paraprofessionals, who hold a minimum of a diploma in animal health. These paraprofessionals operate under the supervision of district or regional veterinarians, who hold a Doctor of Veterinary Medicine (DVM) degree, and assign them specific operational areas to deliver veterinary services [22].

To ensure resource optimization and sustainability of the intervention, this project will leverage the existing veterinary service and local authority framework within the study setting. In collaboration with the veterinary paraprofessionals assigned to the operational areas within which the intervention communities are located, we will identify individuals in each community to receive the intervention (training). The training will be conducted with support from local staff of the Veterinary Services Directorate and the Department of Agriculture in the study districts.

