### Sample size

3.5

The sample size was estimated with the epiDisplay package in R software [28]. With a sample size of 460 farming households across 23 village clusters per treatment group, the study is powered to detect a difference of 25% to 40% vaccination coverage with 80% power, assuming alpha = 0.05, power = 0.8, intra-cluster correlation coefficient = 0.2, and non-response rate = 10%.

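### The livestock-unit conversion in the eligibility rule is stated in the wrong direction, so the minimum herd size as published is not the one apparently meant

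*Protocol article*

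**What the plan says.** Eligibility is set out in section 3.6 (Data collection and management) of the protocol article. The ownership condition is that "farmers need to own at least three (3) tropical livestock units (TLUs) of eligible ruminants", where an eligible ruminant is at least 3 months old. The unit is then defined, with a literature citation: "One (1) TLU corresponds to 0.75 cattle and/or 0.1 small ruminants (sheep and goats". The same minimum also serves as an exclusion rule: "Caretaker farmers who do not own the minimum TLUs of the livestock in the herds kept will be excluded from the study".

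No other part of the article restates the conversion, gives the minimum as a number of animals, or corrects its direction.

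Two other statements bear on the point. The Introduction says that the average market value of ruminant livestock in Africa "ranges between USD 120 for one sheep or goat and USD 600 for one cattle". Section 3.1 (Study setting) says: "Cattle, sheep, and goats are the predominant ruminant livestock species reared in these districts".

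**The concern.** The sentence gives animals per unit, but the two numbers make sense only as units per animal. A unit equal to one tenth of a goat sets the small-ruminant minimum at a fraction of one animal. It also ranks a goat far above a head of cattle.

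The rule fixes the eligible population. Sheep and goats are among the main ruminants in the study districts, so the larger discrepancy falls on a main group of keepers and not on a rare one. Herd size is also relevant to the trial's question. The Introduction names, as a barrier to vaccination, having to pay for a whole vial with too few animals to use it. One form of the primary outcome (section 3.8.1) is the average proportion of animals per herd vaccinated. A reader therefore needs to know the smallest herd that could enter. Someone repeating the trial from the published text would recruit under a different rule from the one apparently meant.

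**Working it through.** **Inputs**
- Minimum holding: 3 TLU (section 3.6).
- Conversion factors: 0.75 for cattle and 0.1 for small ruminants (section 3.6).
- Market values: USD 600 per head of cattle and USD 120 per sheep or goat (Introduction).

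The conversion is a stated definition, so there is no computed figure to reproduce. The check takes the definition in each direction and asks what the minimum becomes.

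**Step 1. As written (factors are animals per TLU).**
- TLU per animal = 1 / factor: cattle 1/0.75 = 1.33; sheep or goat 1/0.1 = 10.
- Animals needed = 3 × factor: cattle 3 × 0.75 = 2.25, so 3 whole animals; small ruminants 3 × 0.1 = 0.3, so 1 whole animal.
- Holdings below the minimum: one head of cattle only (1.33 TLU) or two only (2 × 1.33 = 2.67 TLU). A holding that includes one eligible sheep or goat has at least 10 TLU and passes.
- Implied ranking: 10/1.33 = 7.5, so one goat counts as 7.5 cattle.

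**Step 2. Reversed (factors are TLU per animal).**
- Animals needed = 3 / factor: cattle 3/0.75 = 4; small ruminants 3/0.1 = 30.
- Mixed holdings, rounded up to whole animals: 1 head of cattle + 23 small ruminants (0.75 + 2.3 = 3.05 TLU); 2 + 15 (1.5 + 1.5 = 3.0); 3 + 8 (2.25 + 0.8 = 3.05).
- Implied ranking: 0.75/0.1 = 7.5, so one head of cattle counts as 7.5 small ruminants.

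**Step 3. Compare with the article's own values.** 600/120 = 5, so one head of cattle is worth about five sheep or goats. The reversed reading agrees in direction; the reading as written runs the opposite way.

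**Step 4. Difference in whole animals.**

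| Holding | Minimum as written | Minimum if factors are per animal |
|---|---|---|
| Small ruminants only | 1 | 30 |
| Cattle only | 3 | 4 |

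**The case against.** The strongest reply is that this is a slip of wording. A minimum of 0.3 of a goat is visibly absurd, field staff would hardly apply it, and nothing in the article shows that the screening form did. That is a fair account of the likely cause, and it limits what can be claimed. It does not make the sentence right: this is the only statement of the threshold in the article, and a reader cannot tell from it which rule was used.

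A second reply is that market prices do not define a livestock unit, and that 5 is not 7.5. This also stands in part. The prices support the direction of the conversion only. The first internal sign is independent of them: a minimum that one small ruminant exceeds more than threefold (10 TLU against 3) sits badly with a threshold that is also used to exclude caretakers.

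A third reply is that the head counts of 4 and 30 depend on a cited source not available here, and that section 3.1 describes production dominated by small-scale farmers, so a minimum of 30 small ruminants is not self-evidently the intended one. That stands, and the head counts are conditional on the sponsor's confirmation.

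A reader might also infer more than the article supports:
- That the rule as written excludes almost nobody. Cattle-only owners with one or two head are still excluded, and with no herd-size distribution the excluded share cannot be computed.
- That the threshold is wrong 100-fold. That sets 0.3 of an animal against 30 (30/0.3 = 100). In whole animals it is 1 against 30.
- That the treatment comparison is biased. The ownership rule is the same in both arms, so a looser or tighter threshold does not by itself bias the contrast.
- That the 25% and 40% coverage assumption fails. Section 3.5 lists the remaining inputs ("assuming alpha = 0.05, power = 0.8, intra-cluster correlation coefficient = 0.2, and non-response rate = 10" per cent) and ties none of them to herd size, so such an effect has no figure behind it.

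**Conclusion.** The conversion is wrong as written. The direction of the error follows from the article alone: the unit makes one sheep or goat worth 10 TLU and 7.5 cattle, against the article's own price ratio of about 5 in favour of cattle.

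If 0.75 and 0.1 are TLU per animal, as they appear to be, the minimum for small-ruminant-only households is 30 animals and not 1, and for cattle-only households 4 and not 3. These figures assume that the two factors and the 3-TLU minimum are themselves correct and that only the direction was reversed.

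The consequence is confined to the definition of the eligible population and the generalisability of the results. The number of households affected is unknown. Whether anyone was screened under the literal rule is also unknown, and the article gives no sign that this happened.

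**What to change.** 1. Confirm the two factors against the cited source.
2. If they are confirmed, restate them per animal: one head of cattle = 0.75 TLU; one sheep or goat = 0.1 TLU.
3. Give the threshold in head counts beside the units: 3 TLU = 4 cattle, or 30 small ruminants, or an equivalent mix such as 2 cattle and 15 small ruminants.
4. Check which direction the electronic screening form used, for owners and for caretakers.
5. Report the threshold actually applied. Section 3.3 places the intervention after the baseline survey, and the Discussion says that farmers have already been trained, so recruitment may be complete. If so, correcting the sentence cannot change who was enrolled, and the check in step 4 is what tells readers which population was studied.

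The cost is one rewritten sentence and one check of a form. No new data are needed, and neither the design nor the analysis changes.

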### Data analysis plan

3.7

We will conduct an intention-to-treat analysis using the available case population, i.e. including data for all households with at least one follow-up observation. The analysis would adhere to principles outlined in ICH Statistical Principles for Clinical Trials [30]. Descriptive analysis will be done to assess for balance of key variables in study arms. If there are any imbalances in the key variables, the study team will discuss the findings, and post-hoc analysis conducted in sensitivity analysis.

### The analysis plan for each study outcome (primary and secondary) is described below

3.8

#### Primary outcome

3.8.1

We will compare the proportion of animals and herds of households vaccinated with CBPP and PPR vaccines between the study arms at mid- and- endpoints, relying on data from veterinary registers and the farmers’ follow-up surveys. We will compare the animal vaccination uptake at farm and district levels (average proportion of animals per herd, and average proportion of all herds per district vaccinated with CBPP, and PPR vaccines) between CAVI intervention households and controls, using mixed effect models with the logit function, accounting for villages as random effects.

#### Secondary outcome (SO) 1

3.8.2

The study will compare between the study arms the average antimicrobial usage intensity (usage per animal per month) by farmers in treating animal diseases at mid- and- endpoints, using multilevel Poisson regression models, accounting for the hierarchical structure of the data. We will determine if changes in intensity of antimicrobials used from baseline to end of study is significantly different from zero.

#### SO 2

3.8.3

In this analysis we will compare the percentage of disease-related mortalities in herds for each ruminant species reared, between CCAVI intervention and control households at the endpoint, using mixed effect models with the logit function, and accounting for the hierarchical structure of the data.

#### SO 3

3.8.4

We will also compare the average wellbeing scores of the farmers between the study arms using linear mixed effect models, accounting for the hierarchical structure of the data. Wellbeing on the physical, psychological, social, and environmental domains will be assessed using the WHO Quality of Life BREF tool. The analysis will determine if the changes in farmers’ wellbeing scores from midpoint to end of study is significantly different from zero.

#### SO 4

3.8.5

Registers of trainees and veterinary personnel, and the interview transcripts will be analyzed at mid- and- endpoints, for positive and negative experiences with CCAVI’s implementation, to determine acceptability of CCAVI. We will apply the framework proposed by Hermann et al. [31] to determine scalability.

We will also assess the cost per additional livestock vaccinated, as well as the program’s effectiveness in improving quality of life.

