## Abstract

Infectious animal diseases represent a major constraint to livestock productivity, food security and wellbeing in many developing countries. To mitigate these impacts, farmers frequently use antimicrobials without professional advice, potentially yielding drug residues in livestock products and the food chain, as well as resistant antimicrobial genes. Recent studies identified Contagious Bovine Pleuropneumonia (CBPP) and Peste des Petits Ruminants (PPR) as the diseases most negatively affecting ruminant livestock productivity and farmers’ wellbeing in Ghana. Despite the approval and availability of effective CBPP and PPR vaccines in Ghana, acceptability, affordability, accessibility, and availability of vaccination limit their uptake, with only 15% of farmers regularly vaccinating their herds. During formative qualitative research to identify barriers and potential intervention options, farmers suggested that establishing localized farmer intervention platforms could improve vaccine access. The main idea is the platforms enabling information exchange on livestock vaccines, enhancing service scheduling, and sharing vaccination costs among farmers living in the same locality. We now wish to test formally this hypothesis.

Through a cluster-randomized controlled trial, we aim to determine the effect of localized farmer platforms on animal vaccination uptake (primary outcome), antimicrobials use in livestock production, disease-induced mortality in livestock, and livestock farmers’ wellbeing (secondary outcomes). The intervention will be randomized at the community level. The study will involve 460 farming households across 46 rural communities (study clusters). Clusters will be randomized with equal probability to treatment and control (23 communities each). Approximately 10 households per community will be sampled for data collection at baseline, and at 6 and 12 months post-intervention, following prevailing vaccination schedules. We will conduct an intention-to-treat analysis using the available case population. The findings will inform strategies to tackle the impact of infectious livestock diseases on food security, public health and farmers’ wellbeing.

**Trial registry**: https://pactr.samrc.ac.za/; ID No.: PACTR202405854213937.

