## Research objectives, hypothesis and study outcomes

2

The main objective of the study is to evaluate the effect of an innovative community-led intervention on the uptake of CBPP and PPR vaccines by livestock farmers in Ghana, and evaluate the impact of vaccination uptake on antimicrobial use in livestock farming, disease-induced livestock mortalities and farmers’ wellbeing. The study will be a cluster randomized controlled trial, which will introduce the intervention communities to a new Community Action for Vaccination Initiative (CAVI) that is expected to enable farmers to coordinate their livestock vaccination efforts by leveraging the strengths of the local group.

The study hypothesis is that CAVI has an impact on uptake of animal vaccines in farming communities. We also hypothesize that CAVI will have an impact on the usage frequency and quantity of antimicrobials in livestock production, occurrence of disease-induced animal mortalities, and wellbeing of livestock farmers.

The primary study outcome is the uptake for CBPP and PPR vaccines. The secondary outcomes include frequency and quantity of antimicrobials used by farmers, incidence of livestock herd mortalities due to disease, farmers’ wellbeing on the physical, psychological, social, and environment domains, and the acceptability and feasibility to scale of CAVI to the key stakeholders including farmers and veterinary service providers.

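### The primary outcome is set out as up to eight co-equal comparisons with none named as leading, while the sample size covers a single contrast

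*Protocol article*

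**What the plan says.** Section 2 of the protocol article presents a single primary outcome: "The primary study outcome is the uptake for CBPP and PPR vaccines". It names no unit, no time point, and no rule for combining the two vaccines.

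Section 3.8.1 then says what will be compared: "the proportion of animals and herds of households vaccinated with CBPP and PPR vaccines between the study arms at mid- and- endpoints". Section 3.6 puts the midpoint at 6 months and the endpoint at 12. The next sentence of section 3.8.1 describes uptake at farm level, as the average share of animals per herd, and at district level, as the "average proportion of all herds per district vaccinated with CBPP, and PPR vaccines". The model is a mixed logit model with villages as random effects.

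Section 3.5 contains one calculation: "the study is powered to detect a difference of 25% to 40% vaccination coverage with 80% power", "assuming alpha = 0.05". This is the only place where a significance level appears. The section does not say whether coverage there means animals or herds, which vaccine it concerns, or at which time.

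**The concern.** A trial with one primary outcome should have one answer to the question of whether the intervention worked. Here the results can disagree: PPR uptake may rise while CBPP uptake stays flat, the share of animals may rise while the share of herds does not, or an effect may show at 6 months and not at 12. The text does not say which of these counts.

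Disagreement is plausible. CBPP concerns cattle and PPR concerns sheep and goats, so the two vaccines go to different animals. The two times also differ in substance, because section 3.3 reinforces the package at 6 months, so the midpoint result precedes full delivery.

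At stake is either the error rate, if a favourable result can be picked from the set, or the power, if every result has to succeed. The sample size allows for neither.

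**Working it through.** **Step 1. Count the comparisons.** From section 3.8.1: 2 units × 2 vaccines × 2 times = 8, if every cell is tested separately. If the vaccines are combined, or both times enter one model with one test, the count is 8 / 2 = 4. With both simplifications it is 2.

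**Step 2. The plan's own figure.** Inputs from section 3.5 are 25% against 40%, alpha 0.05 (taken as two-sided, since sidedness is not stated), 80% power, intra-cluster correlation 0.2 and 10% non-response. Section 3.5 also gives the size: "With a sample size of 460 farming households across 23 village clusters per treatment group". The abstract gives about 10 households per community.

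- Per arm, individually randomised: n = [1.96·√(2 × 0.325 × 0.675) + 0.842·√(0.25 × 0.75 + 0.40 × 0.60)]² / 0.15² = 152.
- Design effect: 1 + (10 − 1) × 0.2 = 2.8.
- Total: 152 × 2.8 = 425.6, rounded up to 426 per arm, so 852. After non-response, 852 / 0.9 = 947.
- Power with 23 × 10 = 230 households per arm (effective 230 / 2.8 = 82) is about 54%.

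The 460 households therefore do not reproduce from the stated inputs, even for one comparison. That is a separate point. It matters here because there is no spare power to pay for several comparisons.

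**Step 3. If any one comparison may count at an unadjusted 5%.** For k independent tests, the chance of at least one false positive is 1 − 0.95^k. For correlated tests I took equally correlated normal statistics and a cut-off of |Z| > 1.96. The article gives no correlations, so these are assumed.

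| Correlation | 8 tests | 4 tests |
|---|---|---|
| 0 | 33.7% | 18.5% |
| 0.5 | 25% | 16% |
| 0.7 | 19% | 13% |
| 0.9 | 12% | 9% |
| 0.95 | 9.5% | 8% |

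For two tests the independent figure is 1 − 0.95² = 9.8%. Because the vaccines concern different species, a correlation near 1 across all cells is unlikely.

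**Step 4. If all comparisons must be significant.** The false-positive rate does not exceed 5%. Joint power cannot exceed that of the weakest comparison. Granting each comparison the planned 80%, joint power for eight lies between 0.80⁸ = 17% (independent) and 80% (perfectly correlated). Anything short of perfect correlation puts it below the 80% claimed.

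**Step 5. If alpha is split.** Bonferroni over eight gives 0.05 / 8 = 0.00625 per test. At 230 households per arm, power for 25% against 40% falls from about 54% to about 24%, and the total needed rises from 852 to 1,390 before non-response. Over four tests (0.0125) power is about 33%; over two (0.025), about 42%.

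**The case against.** The strongest reply is that the article does not state an inflated error rate. The level 0.05 stands only in the sample-size sentence; section 3.8.1 attaches no level to any comparison and never says that one significant result is enough. A multiplicity rule may sit in an analysis plan that is not shown, and section 3.7 commits the analysis to ICH statistical principles. This stands. The absence of an adjustment is not the finding, and the percentages in step 3 are conditional.

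The reply does not remove the core. Which measure and which time point are primary belongs in the protocol, and this article fixes several as equals instead of leaving them open. It can be specific: secondary outcome 2 names the endpoint alone and works species by species.

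Four stronger readings are tempting but not supported.

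- A reader might infer that each comparison is tested at 5% and that any one of them wins. The text says neither.
- A reader might count farm and district levels as a further split and arrive at more than eight. The sentence pairs farm level with animals per herd and district level with herds per district, which restates the two units. Taking the registers and surveys together as one data source, eight is the fullest count, not the minimum.
- A reader might conclude that the arms will be tested on three districts. The stated model compares households with villages as random effects; the district phrase is loose wording for a summary.
- A reader might assume that households without cattle count as unvaccinated against CBPP, or those without sheep or goats as unvaccinated against PPR. The article does not define the denominators that way. It leaves them open, and exact denominators are ordinary analysis-plan detail.

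**Conclusion.** The point holds in a conditional form. The article names one primary outcome and sizes one coverage contrast, yet sets out up to eight co-equal comparisons without saying which one decides. If any may count at an unadjusted 5%, the false-positive rate is about 10% to 34% for eight (correlation 0.95 down to 0) and about 9% to 19% for four (correlation 0.9 down to 0). If all must succeed, alpha is safe and joint power is below that of the contrast sized. A Bonferroni split over eight leaves about 24% power.

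The count of eight assumes separate tests in every cell. The error rates assume an any-one rule and equal correlations, and the power figures assume a two-sided test with 10 households per cluster. None of these assumptions is needed for the basic defect, which is that conflicting results could not be resolved from the text. It should be corrected.

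**What to change.** Before outcome data are seen:

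- Name one primary comparison at 12 months, CAVI against control, two-sided 0.05, using the coverage measure meant in section 3.5. One candidate is a household's herd being vaccinated against the disease or diseases of the species it keeps. Section 3.5 does not say that this was the measure sized, so the authors must confirm or choose.
- State in section 3.5 that this is the outcome on which the sample size rests.
- Make vaccine-specific coverage at 12 months secondary, either in a fixed order or with Holm's adjustment: CBPP among households that keep cattle, PPR among those that keep sheep or goats.
- Label animal-level proportions and all 6-month results as supportive.
- Report coverage by district descriptively.

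This changes wording only and needs no new data. The cost is that fewer results can be called confirmatory.

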Since blinding is not possible, to reduce potential imbalance in dropouts between study arms and non-blinding bias, each participating farmer in the surveys in both study arms would also receive a total of GHC 50 mobile airtime over the three rounds of the survey (baseline, mid-point and end-point follow-ups) as an attention control intervention. The trained individuals will be supported to establish their respective local platform of farmers within the intervention communities, and schedule vaccination visits with veterinary personnel. The veterinary personnel will be provided with registers to record all vaccination requests received from farmers, the number of requests honored (in both study arms), and any adverse events following vaccination. In collaboration with the regional veterinary services directorates and district veterinary personnel, the study will ensure that an adequate supply of vaccines and consumables are maintained at the district level to meet the anticipated demand for vaccination services. Additionally, each veterinary personnel will receive quarterly airtime vouchers worth GHC 50 to support their efforts in delivering vaccination services.

A radio sensitization program will be held to inform all livestock farmers in both study arms about the vaccines availability. The program will be broadcast live on local radio stations in each study district, and the recordings repeated over two weeks prior to intervention implementation to sensitize the communities. The broadcasts will be done in the local languages by veterinary personnel in the study districts, with support from the research team. Fig. 3 below shows the theory of the intervention effect.

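### Antimicrobial use (SO1): the added test of change from baseline against zero states no arm contrast, so its result could not be attributed to CAVI

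*Protocol article*

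**What the plan says.** Section 2 of the protocol article frames the question as an effect of the intervention: "We also hypothesize that CAVI will have an impact on the usage frequency and quantity of antimicrobials in livestock production".

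Section 3.8.2 (SO1) gives two analyses.

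- **Arm comparison.** "The study will compare between the study arms the average antimicrobial usage intensity (usage per animal per month", at mid- and endpoint, "using multilevel Poisson regression models, accounting for the hierarchical structure of the data".
- **Change test.** "We will determine if changes in intensity of antimicrobials used from baseline to end of study is significantly different from zero".

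Section 3.6 provides the baseline measurement: "At baseline, we will collect data on antimicrobial use on animals (frequency and quantity used per month". Section 3.7 adds a descriptive check of balance on key variables, without listing them, and says: "If there are any imbalances in the key variables, the study team will discuss the findings, and post-hoc analysis conducted in sensitivity analysis".

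Section 3.3 describes support that is not confined to the intervention arm: "A radio sensitization program will be held to inform all livestock farmers in both study arms about the vaccines availability". The same section has the study maintain vaccine supply at district level. Section 3.2 stratifies randomization by district, so that supply serves communities in both arms.

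Section 3.8.4 (SO3) uses the same change-from-zero form for wellbeing scores, from midpoint to end.

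**The concern.** The hypothesis concerns what CAVI does to antimicrobial use, and only a contrast between randomized arms answers that. The first SO1 sentence names the arms and the second does not. Taken as written, the second asks whether use moved over the year. Use can move for reasons common to both arms: the radio programme, better vaccine supply, repeated surveys or a change in disease pressure.

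Two things are at stake. First, a significant fall from baseline could be reported as support for CAVI when both arms fell alike. Second, the baseline antimicrobial data are the natural means of sharpening the arm comparison, yet the only analysis that names them is one that cannot speak to CAVI.

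**Working it through.** **Reading the two sentences together.** The arm comparison at follow-up is concurrent and randomized, so drift common to both arms cancels. The change test has zero as its reference and no control term, so common drift goes straight into the result.

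**How far apart the two can be.** The article gives no rate, SD, correlation or design figure for antimicrobial use, so there is no stated figure to reproduce. The calculation below is illustrative.

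Inputs from the article:
- k = 23 communities per arm, about 10 households each (Abstract).
- Non-response 10% (section 3.5), so m = 10 × 0.9 = 9 households per community.
- Intra-cluster correlation 0.2, borrowed from section 3.5, where it refers to vaccination coverage.

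Assumed inputs:
- Log-scale SD of use, s = 0.8 to 1.2.
- Baseline-endpoint correlation r = 0.3 to 0.7, the same at community and household level.
- No CAVI effect, and the same proportional fall in both arms.

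Formulas (normal approximation, two-sided 5%):
- Between-community variance B = 0.2 × s²; within-community variance W = 0.8 × s².
- Variance of one arm's mean log change: V = [2B(1 − r) + 2W(1 − r)/m] / k.
- Standard errors: one arm √V; both arms pooled √(V/2); difference between arms √(2V).
- P(significant) = Φ(−1.96 − δ/SE) + 1 − Φ(1.96 − δ/SE). Here δ = ln(1 − fall) for the change test and δ = 0 for the arm contrast.

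One case in full (s = 0.8, r = 0.5, common fall 20%):
- B = 0.2 × 0.64 = 0.128; W = 0.8 × 0.64 = 0.512.
- V = (0.128 + 0.0569)/23 = 0.00804; √V = 0.0897.
- δ = ln 0.8 = −0.223. One arm: δ/SE = −2.49, P = 0.702.
- Pooled: SE = 0.0634, δ/SE = −3.52, P = 0.941.
- Arm contrast: δ = 0, P = 0.05.

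| Common fall | s | r | One arm vs zero | Pooled vs zero | Between arms |
|---|---|---|---|---|---|
| 10% | 0.8 | 0.3 | 0.168 | 0.290 | 0.05 |
| 10% | 0.8 | 0.5 | 0.217 | 0.383 | 0.05 |
| 10% | 0.8 | 0.7 | 0.329 | 0.574 | 0.05 |
| 10% | 1.2 | 0.3 | 0.102 | 0.155 | 0.05 |
| 10% | 1.2 | 0.5 | 0.123 | 0.198 | 0.05 |
| 10% | 1.2 | 0.7 | 0.173 | 0.299 | 0.05 |
| 20% | 0.8 | 0.3 | 0.557 | 0.845 | 0.05 |
| 20% | 0.8 | 0.5 | 0.702 | 0.941 | 0.05 |
| 20% | 0.8 | 0.7 | 0.895 | 0.995 | 0.05 |
| 20% | 1.2 | 0.3 | 0.289 | 0.509 | 0.05 |
| 20% | 1.2 | 0.5 | 0.382 | 0.650 | 0.05 |
| 20% | 1.2 | 0.7 | 0.572 | 0.858 | 0.05 |

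**What the baseline could do instead.** Relative to the follow-up comparison without baseline, the variance of the arm contrast is multiplied by about 1 − r² if adjusted for baseline, and by 2(1 − r) if taken as a simple difference in change.

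| r (assumed) | Baseline-adjusted: 1 − r² | Difference in change: 2(1 − r) |
|---|---|---|
| 0.3 | 0.91 (9% lower) | 1.4 (40% higher) |
| 0.5 | 0.75 (25% lower) | 1.0 (no change) |
| 0.7 | 0.51 (49% lower) | 0.6 (40% lower) |

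Both forms are attributable to CAVI. Only the adjusted form gains precision across the whole range.

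**The case against.** **The lead analysis is sound.** A reader might infer from the change sentence that antimicrobial use is judged by an uncontrolled before-after test. The document does not support that. The preceding sentence plans a randomized comparison at both follow-ups, which keeps its level when use drifts in both arms. The change test is an addition. This objection stands and limits the point to the added test.

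**The sentence may have meant an arm contrast.** It follows directly on the between-arm model, and the changes could mean the difference in change between arms. That is possible, but the text does not say so; if it was meant, it should be written. A reader might also infer that each arm will be tested separately and the p-values compared. Nothing in the article plans that.

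**Leaving baseline out is not an error.** The unadjusted randomized comparison is unbiased, and covariates are commonly left to an analysis plan that is not shown. This stands: the gain from adjustment is a reason to choose that form of repair, not a separate fault.

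**The Poisson model.** Section 2 lists "frequency and quantity of antimicrobials used by farmers" as the outcome, so a reader might infer that drug quantity in grams or milligrams will be forced into a count model, with precision that depends on the unit. The article never says that quantity enters that model and names no unit; treatments per animal-month would be a natural Poisson rate. How quantity will be modelled is unclear, but that is a detail for the analysis plan and not a shown error.

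**Conclusion.** The point holds in a limited form. SO1 has a valid between-arm comparison, to which the article adds a significance test of change from baseline with no arm contrast stated. Read literally, that test cannot be attributed to CAVI, because sensitization and vaccine supply reach both arms.

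The size depends on assumptions that the article neither gives nor contradicts. For a shared 20% fall and no CAVI effect, the test would be significant with probability 0.29 to 0.90 in one arm and 0.51 to 0.995 pooled. For a shared 10% fall the ranges are 0.10 to 0.33 and 0.16 to 0.57. A between-arm contrast stays at 0.05. If use does not drift, the change test has no such excess.

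This concerns one added analysis of a secondary outcome and leaves the planned arm comparison intact. It is still worth correcting, because a false claim of reduced antimicrobial use is easily made from such a test and the repair is nearly free.

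**What to change.** In section 3.8.2, replace the change-from-zero sentence with a between-arm contrast, in one of two forms:

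- the CAVI/control ratio of use at follow-up, adjusted for the household's baseline use, within the planned multilevel model; or
- an arm-by-time term in that model, with baseline as one of the time points.

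The first is preferable on precision, as shown above. Report any within-arm change as descriptive, without a test.

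In section 3.8.4 (SO3), restate the midpoint-to-end change as a difference between arms in the same way. Section 3.6 lists wellbeing from midpoint onward and not at baseline, and section 3.3 delivers the intervention before midpoint. The midpoint score is therefore an outcome and should not serve as a baseline covariate.

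The cost is a few lines of analysis wording. The baseline antimicrobial data are already in the collection plan, and neither the sample nor the schedule changes.
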